## Trial status

The project is planned from January 2019 until December 2020. The recruitment phase of this study is scheduled from January 2020 to March 2020. The intelligent household added salt monitoring system will be developed and improved from January 2019 until December 2019. The daily added salt intake of each household member will be monitored from April to September and the salt consumption-related KAP of the household main cook will be investigated in April, July and October 2020. Data analysis and evaluation will be performed after September 2020. The protocol stands at version 3.0 on 10 March 2020.

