**Fig. 1 Fig1:**
[figure not shown]
System functional structure diagram

The front-end sensing system is also called the “smart salt checker”. It has a salt container and an electronic salt sensor. The electronic salt sensor is equivalent to a self-designed electronic weighing scale on the base of the salt container, which can weigh the salt in the container, with a weighing range of 0–250 g and a sensitivity of 0.2 g. After the user takes the salt each time, and the container is placed on the base with the lid closed, the processing unit of the electronic salt sensor can immediately detect and record the weight and the time of salt used.

The cloud analysis system can automatically calculate the individual added salt intake of each household member according to the information acquired from the terminal interaction system. The daily added salt intake of each household member will be calculated on the basis of the distribution of staple food consumption of residents in the household. Daily intake estimates of added salt for each household member (g/standard) = (30 days’ intake of added salt by the surveyed household × standard daily number of each member in the household/standard daily number of all people in the household)/30 [39].

The terminal interaction system is a salt-limiting WeChat mini programme; through the programme, basic data can be acquired of the participating household’s main cook and other household members, such as their age, gender, occupation, marital status, education level, height, weight, labour intensity, health status, the number of people per meal and meal ratio per day for members aged>2 years old in their household. Participants with hypertension will also be encouraged to provide data on blood pressure, and the time and tool of blood pressure measurement.

Overall, the SALTCHECKER contains three key features: (1) self-monitoring: to automatically calculate the daily added salt intake of each household member, (2) questionnaires: to investigate the basic demographic information of the household’s main cook and other household members and salt consumption-related KAP of the household’s main cook, (3) personalised reports: through salt-limiting WeChat mini programme, professional nutrition experts in our research group will provide the daily added salt intake of each household member and corresponding healthy salt-using suggestions for specific household members to the household’s main cook.

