### Procedure

A baseline survey will obtain the household demographic information and the salt consumption-related KAP of the household’s main cook. In the test period, the household’s main cook in the intervention group will use the smart salt checker and the salt-limiting WeChat mini programme, while the household’s main cook in the control group will use the smart salt checker with only the weighing function. The data of the daily added salt intake of each household member will be automatically calculated using SALTCHECKER. And the salt consumption-related KAP of the household’s main cook will be assessed at the beginning of the test (i.e. at baseline), the third month and the sixth month after the test. Finally, the effect of the household added salt monitoring system will be evaluated by changes in daily added salt intake of each household member and the salt consumption-related KAP of the household’s main cook. The technological roadmap is shown in Fig. 2.

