### Baseline survey

#### Daily added salt intake of each household member

The front-end sensing system in the SALTCHECKER will automatically obtain the data of the added salt consumption of participating households, and the data will be collected and stored every day. The daily added salt intake of each household member will be calculated based on a formula, described in the Development of SALTCHECKER stage 1 section.

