#### Randomization and blinding

After the baseline survey, 600 participating households’ main cooks will be randomly divided following a 1:1 ratio into the intervention group and the control group by the household demographic information, with 300 households in each group. The study coordinator will be responsible for the randomization and verification of the computer-generated intervention assignment with a randomization table. All the investigators, except for the study coordinator, will be blinded. The participants will be blinded and instructed not to inform the other participants of the treatment they receive.

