### Intervention

#### Intervention group

In the intervention period, the participating household’s main cook in the intervention group will install the smart salt checker in their households, and receive the personalised reports and health education through the salt-limiting WeChat mini programme monthly. Personalised reports will mainly contain the daily added salt intake of each household member, the adverse impact of excessive salt consumption and the salt-limiting suggestions. The health education includes salt-limiting guidance and targeted health articles. The salt-limiting guidance will be provided by professional nutrition experts through the salt-limiting WeChat mini programme. People from the target population can select the intervention content depending on their specific situations and interests. The participating household’s main cook can propose questions and ask for suggestions from the nutrition experts in real time through the WeChat mini programme. The intervention period will last for 6 months. Through the personalised reports and health education, we seek to provide the participating household’s main cook with useful and effective guidance on two aspects:
Provide the daily added salt intake of each household member.Convey knowledge and suggestions on the negative effects of excessive salt consumption and ways to limit salt consumption and maintain healthy behaviour.

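### Salt monitoring from April to September cannot supply both a 30-day baseline before randomisation and a salt value at 6 months of intervention

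*Protocol article*

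**What the plan says.** All references are to the protocol article.

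- *Primary outcomes*: daily added salt intake of each household member is assessed at baseline, 3 and 6 months.
- *Baseline survey, Daily added salt intake of each household member*: the source is the device. "The front-end sensing system in the SALTCHECKER will automatically obtain the data of the added salt consumption of participating households", and the value is worked out with the formula from Stage 1.
- *The Development of SALTCHECKER*: the numerator of that formula is "30 days’ intake of added salt by the surveyed household", shared among members and divided by 30.
- *Randomization and blinding*: "After the baseline survey, 600 participating households’ main cooks will be randomly divided".
- *Procedure*: "A baseline survey will obtain the household demographic information and the salt consumption-related KAP of the household’s main cook". Use of the checker is described for the test period, and the KAP baseline is equated with the beginning of the test. The effect is to be judged by changes in salt intake and KAP.
- *Intervention group*: within the intervention period, "the participating household’s main cook in the intervention group will install the smart salt checker in their households". Also, "The intervention period will last for 6 months".
- *Trial status*: "The recruitment phase of this study is scheduled from January 2020 to March 2020". Then "The daily added salt intake of each household member will be monitored from April to September". KAP is surveyed in April, July and October 2020, and the project ends in December 2020. No date is given for randomisation or for the start of the intervention.

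**The concern.** A baseline for a randomised comparison should be measured before allocation. Here it takes 30 days of checker data, so the checker has to run in every household for about a month before randomisation. The calendar schedules no salt monitoring in the recruitment months, and the monitoring that starts in April lasts only as long as the intervention. *Procedure* and *Intervention group* place the checker in the test or intervention period, whereas *Baseline survey* and *Randomization and blinding* imply that it is already recording before allocation.

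One of two things is at stake. If the first salt value is taken under treatment, it may already contain part of the effect, and subtracting it shrinks the difference between arms. If April is kept free of treatment, the salt outcome has no value at 6 months of intervention. Both are stated time points of a primary outcome.

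**Working it through.** **Inputs**

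| Input | Value | Where |
|---|---|---|
| Averaging window of the intake formula | 30 days | The Development of SALTCHECKER |
| Formula applied to baseline | yes | Baseline survey |
| Randomisation | after the baseline survey | Randomization and blinding |
| Intervention length | 6 months | Intervention group |
| Salt monitoring | April to September 2020 | Trial status |

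The protocol gives no day count of its own to reproduce; the check is a count of calendar days.

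**Step 1. Days available.** April to September = 30 + 31 + 30 + 31 + 31 + 30 = 183 days, or 6 calendar months.

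**Step 2. Days needed.** A 30-day baseline plus 6 months of intervention. Six months are 183 days (April to September) or 184 days (May to October), so 30 + 183 = 213, or 30 + 184 = 214.

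**Step 3. Shortfall.** 213 − 183 = 30 days, or 214 − 183 = 31 days.

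**Step 4. Can a start date rescue it?** Let the intervention start k days after 1 April. Then k days are monitored before it and 183 − k days during it.

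| Intervention starts | Days before | Monitored days on intervention | What fails |
|---|---|---|---|
| 1 April (k = 0) | 0 | 183 | No baseline before allocation; first 30-day value lies in treatment month 1 |
| 8 April (k = 7) | 7 | 176 | Both: baseline under 30 days, end of month 6 not reached |
| 15 April (k = 14) | 14 | 169 | Both, as above |
| 1 May (k = 30) | 30 | 153 of 184 | Last 31 days (all of October) unmonitored; salt data end at month 5 |

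The baseline needs k of at least 30, and the 6-month value needs k = 0. No start date within the window satisfies both.

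**Step 5. Consequence if treatment starts on 1 April.** Let δ be the true difference between arms at a later visit and f the share of it already present in the first 30 days. The difference in change from baseline is δ − fδ = (1 − f)δ, so the share lost is f. With regression adjustment on the same value with coefficient b, what remains is (1 − bf)δ, so the loss depends on b as well. The documents give no value for f. A direct comparison of arms at 3 or 6 months estimates δ and is not affected.

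**Step 6. Consequence if treatment starts on 1 May.** The baseline is clean and there is no such loss, but the last salt value is a 5-month value.

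**Step 7. Do the KAP months decide between the readings?** No. From a 1 April start, 3 and 6 months are reached at the turn to July and to October. From a 1 May start, they are reached on 31 July and 31 October. Surveys in April, July and October fit either.

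**The case against.** The strongest reply is that the text on sequence points to a proper baseline: salt intake stands under the Baseline survey heading and randomisation comes afterwards. The Procedure summary of the baseline survey need not be exhaustive. The Quality control section also has the developer run a test operation in participating households before the study, so installing the device in the intervention period need not mean its first placement. Figures 2 and 3, which hold the roadmap and the schedule, are not visible in the text reviewed and may show the dates.

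Much of this stands. A reader might infer that baseline salt intake is definitely measured under treatment. The documents do not support that as a fact: with no date for randomisation or intervention start, it is one of two readings, suggested by Procedure and Intervention group and opposed by Baseline survey and Randomization and blinding. It does not remove the conflict, because the sequence text only moves the failure to the 6-month point. The test operation is not described as collecting intake data, and Trial status dates salt monitoring from April.

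A second reply concerns harm. Personalised reports and health education are monthly, so little may reach households in the first 30 days and f could be near zero. This is fair, although cooks can question the nutrition experts in real time, and the Discussion adds weekly prompts and daily reminders. Both arms have the weighing device, so only the effect of the mini programme would be lost from the contrast between arms. The Discussion expects a larger effect from baseline to 3 months than later, but says nothing about the first 30 days and gives no basis for a figure.

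Third, Stage 2 compares the arms at each time point and the Analysis strategy does not commit to a change score. That is correct: only the change-based evaluation in Procedure is exposed. A reader might also infer that a subgroup of over-consuming households, defined at baseline, is spoilt. Such households appear only as an expectation in the Discussion, without a definition, and no subgroup analysis of them is named.

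**Conclusion.** As stated, the calendar cannot deliver the salt primary outcome at all its time points. It is 30 to 31 days short of the 213 to 214 needed. This rests on taking April to September as whole months, on the 30-day formula applying to baseline as the Baseline survey section says, and on 6 months meaning calendar months.

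Which time point fails is not settled by the text. If the intervention starts on 1 April, there is no salt baseline before allocation and an analysis of change loses a share f of the effect, of unknown size and possibly small. If it starts on 1 May, the baseline is sound and the 6-month salt value is missing by about one month. Neither a demonstrated bias nor a numerical loss can be claimed. This should be fixed; it does not undermine a direct comparison of arms at the follow-up visits that fall within the monitored period.

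**What to change.** **Preferred.** Run the checker in weighing-only mode in all 600 households for 30 days before randomisation and take that window as baseline salt intake. Count the 3- and 6-month windows from randomisation, and extend salt monitoring by about one month. For example, with baseline in April and intervention from 1 May to 31 October, 30-day windows ending at 3 and 6 months would be 2 to 31 July and 2 to 31 October, the months in which KAP is already surveyed. The cost is about one more month of monitoring with devices already supplied. Analysis would start after October instead of after September, within a project that runs to December 2020.

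**If the calendar cannot move.** State that there is no salt baseline before allocation, remove it from the salt outcome, and compare the arms directly at 3 and 6 months from a 1 April start, without subtracting or adjusting for the first treatment month. This needs wording only; the price is the precision that a true baseline covariate might have added.

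**In either case.** Give the dates of baseline salt measurement, randomisation and intervention start. Reconcile The Development of SALTCHECKER (formula), Procedure, Baseline survey, Randomization and blinding, Intervention group, Primary outcomes and Trial status with them.

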## Data Availability

The data sets used and/or analysed during the current study will be available from the corresponding author on reasonable request.
